| Dropout/Removal Criteria | - 1. Participants who do not meet the screening criteria;   2. Participants who are unable to evaluate for efficacy or unable to evaluate safety without receiving 1 dose of the drug;   3. Participants who are treated with chemotherapy, surgical or experimental drugs other than this protocol during the trial;   4. Participant's concurrent use of China Food and Drug Administration (CFDA)-approved modern herbal agents and immunomodulatory agents for the treatment of tumors;   5. Participants who do not follow the dose, method, and course of treatment according to the study protocol. |
| Termination Criteria | Subject must termination the study if the following cases occur (including but certainly not limited to):   - 1. Disease progression (PD) determined according to RECIST 1.1 criteria or considered clinically progressive.   2. Termination of treatment decided by the investigator from the patient's best interests.   3. Occurrence of intolerable adverse reactions or severe adverse events confirmed by the investigator.   4. Patients with poor compliance, using drug amounts outside the range of 80% to 120% of the prescribed dose.   5. Patient withdrawal of informed consent.   6. Initiation of other anti-tumor drug treatments affecting efficacy judgment (such as chemotherapy, targeted therapy, or biologic agents).   7. Unexpected pregnancy. |
| Study Schedule | Estimated date of the start of the study: August 2019  Estimated enrollment date of the last subject: August 2020  Estimated date of the end of the study: August 2021 |
| Study Procedures | TQB2450 plus anlotinib hydrochloride capsules were administered in a 21-day cycle until disease progression or intolerance. |
| Primary effect endpoints | Duration of response (DoR); overall survival (OS); 12-month progression-free survival rate; disease control rate (DCR); objective response rate (ORR) (assessed per RECIST version 1.1 at the following time points: 3 weeks after the first therapy, then every 6 weeks thereafter during therapy.) |
| Primary safety endpoints | Dose-limiting toxicities (DLT); maximum tolerable dose (MTD); vital signs; laboratory index; adverse event (AE); immune-related adverse event (irAE); serious adverse event (SAE) according to NCI CTCAE version 5.0. |

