     1. Decisions to withdraw from the study by the investigator

The investigator has the right to decide whether to withdraw from the study if a subject who has been enrolled in the study has any situation that is not suitable for continuing the study:

1. Participants who do not meet the screening criteria;
2. Participants who are unable to evaluate for efficacy or unable to evaluate safety without receiving 1 dose of the drug;
3. Participants who are treated with chemotherapy, surgical or experimental drugs other than this protocol during the trial including CFDA-approved modern herbal agents and immunomodulatory agents for the treatment of tumors
4. Participants who do not follow the dose, method, and course of treatment according to the study protocol with poor compliance using drug amounts outside the range of 80% to 120% of the prescribed dose.
5. Occurrence of intolerable adverse reactions or severe adverse events confirmed by the investigator.
6. Termination of treatment decided by the investigator from the patient's best interests.
   - 1. Decisions to withdraw from study by the subject

According to the CIF, the subjects participate in the trials voluntarily and have the right to withdraw at any stage of the trial without discrimination or retaliation and without affecting their medical treatment, rights, and interests; participants who were no longer receiving medications, leading to lost to follow-up without explicit withdrawal from the study, are considered as “withdrawal” or “dropout”. There are possible reasons for withdrawal from study:

- 1. Patient withdrawal of informed consent.
  2. The patient lost to follow-up for various reasons
     1. Subsequent data collection

The investigator must clearly document the reasons and timing for a participant's withdrawal, perform relevant observations and evaluations, complete the assessment according to the study's withdrawal criteria, and record these details in the relevant source documents, detailing the cause of withdrawal.

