For the anlotinib hydrochloride capsules that have been distributed to the subjects, the remaining drugs of the last time should be recalled. For the drugs that have not been distributed to the subjects, they should be handed over to the co-organizers for disposal or destruction after the end of the trial together with the remaining drugs recovered during the trial.

- 1. **TQB2450preparation method**

Aseptic principles should be strictly followed during the preparation process. Under aseptic conditions, extract the desired dose of TQB2450from the glass bottle and aseptically dilute it with sterile, non-heated physiological saline to a total volume of 250ml in an infusion bag. Gently invert the solution without shaking to ensure adequate mixing.

As an injectable medication, it should be visually inspection for the presence of particulate matter and discoloration before administration. The drug is a clear to slightly opalescent, colorless to pale yellow liquid. If the solution appears cloudy, discolored, or in the presence of visible particles, it should be discarded. Do not shake the vial.

TQB2450 does not contain preservatives and IV bags containing TQB2450 must be used immediately after dilution/mixing. If the TQB2450 dilution cannot be used immediately, the method of storage is as follows:

- The total storage time from opening the TQB2450 vial to the end of injection should not exceed 6 hours at room temperature;
- The total storage time should not exceed 24 hours in the refrigerator of 2 ℃-8 ℃ without freezing and shaking.
  1. **Administration regimens of the study drugs**
     1. **Administration principles**

During the study period, every 21 days will be one treatment cycle. More than 3 days per treatment cycle will be considered as reasonably delayed dosing, the subsequent administration time was calculated according to the actual date of the previous administration. No other anticancer therapy was allowed during the medication. Patients with the disease control (CR+PR+SD) and who can tolerate adverse effects continue the medication until disease progression or intolerance.

- TQB2450: On the first day of each cycle (D1), a fixed dose of 1200mg will be administered intravenously using an infusion set with a filter membrane, and infused for 60 ±10 minutes. The infusion time starts with the beginning of the TQB2450 infusion and ends with the completion of the TQB2450 infusion and normal saline flushing.

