**Table 5.5-1 Adjustment measures for infusion reaction**

| Grades of AEs  (NCI-CTCAE v5.0) | Adjustment measures |
| --- | --- |
| Grade 1- mild  It is not recommended to interrupt the infusion and clinical intervention for transient mild reactions | The rate of drop was reduced by 50% and any worsening symptoms were closely observed, and clinical intervention was performed if necessary. |
| Grade 2- moderate  Treatment or fluids should be suspended and systemic therapy (e.g., antihistamines, nsaids, anesthetics, intravenous fluids) should be given immediately. Prophylactic therapy is recommended for 24 hours or less. | Treatment with TQB2450 was suspended and resumed when the infusion reaction had resolved to grade 0-1 with a 50% reduction in the infusion rate. During this period, any worsening symptoms were closely observed and appropriate therapeutic interventions were initiated according to local medical practices. |
| Grade 3- severe  Symptoms persist, such as a slow response to systemic therapy and suspension of infusions, relapses after rapid resolution, and hospital admission due to complications. | Treatment with TQB2450 was immediately and permanently discontinued, and appropriate therapeutic interventions were implemented according to local practice. |
| Grade 4- life-threatening and requiring urgent medical intervention |  |

If the infusion rate of TQB2450 is reduced by 50% (90±10min) because of an infusion reaction, this reduction must be maintained for the next scheduled infusion. If an infusion reaction was not observed at the next scheduled infusion, the infusion rate could be returned to the baseline rate during subsequent infusions.

- - 1. **Adjustment of administration regimens**
       1. **General principles for adjustment of administration regimens**

When a toxic reaction occurs, the investigator may refer to the following rules for delay or dose adjustment. The reason for the delay or dose adjustment, the supportive therapy taken and the results should be documented in the subject's medical record and EDC.

If the investigator determines that the dosing adjustment differs from the proposed adjustment rule, after consultation and communication with the sponsor, the investigator will make the appropriate adjustment with reference to clinical practice guidelines or previous clinical experience, and the relevant reasons will be recorded in the subject’s medical record.

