- Toxic reactions should be graded according to the NCI CTCAE 5.0;
- In case of simultaneous occurrence of severe toxicity of different severity levels, adjustments should be made according to the highest level observed;
- Treatment delays due to toxicity caused by anlotinib capsules could be delayed up to 35 days after the start of day 1 of the cycle (i.e., a 14-day delay in planned treatment) to allow adequate time for the subject to recover from any toxic effects caused by anlotinib hydrochloride. If a subject is unable to resume treatment by day 35 after the last dose, the subject must discontinue anlotinib hydrochloride treatment;
- Treatment delays due to toxic reactions caused by TQB2450 could be delayed up to 12 days after the start of day 1 of the treatment cycle;
- If subjects require permanent discontinuation due to toxic reactions (e.g., immune-related pneumonitis) of TQB2450, monotherapy with anlotinib should be continued until disease progression or unacceptable toxicity (whichever occurs first);
- If subjects require permanent discontinuation due to toxic reactions (hypertension, proteinuria, etc.) of anlotinib, monotherapy with TQB2450 should be continued until disease progression or unacceptable toxicity (whichever occurs first);
  - - 1. **Criteria for Dose Delay**

All of the following conditions should be met before starting treatment in any cycle, otherwise, a delay in administration is required:

- Absolute neutrophil count ≥1.5×109/L;
- Platelet count ≥75×10^9^/L;
- Hemoglobin（Hb）≥80g/L;
- Proteinuria ≤2+;
- Hand-foot skin reaction and hypertension ≤grade 2;
- Other toxicities until recovery to ≤grade 1

During the administration period (1-14 days) of anlotinib every cycle, if toxic reactions occur and the medication needs to be delayed, the maximum delay time should not exceed 5 days. If the medication cannot be continued for more than 5 days, the remaining anlotinib will not be administrated in this cycle.

- - - 1. **Dose modification**

Dose modifications for the TQB2450 were not allowed in principle throughout the study.

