For anlotinib hydrochloride capsules, according to the 3+3 dose climbing test, the maximum tolerated dose was determined as the initial dose. If the initial dose is 12mg, dose level 1 is 10mg, and dose level 2 is 8mg; If the initial dose is 10mg, dose level 1 is 8mg; If the initial dose is 8mg, there was no down-dose selection. Any subject who required a reduction in the anlotinib capsule dose would continue to receive the reduced dose for subsequent cycles. Any subject who has undergone two dose reductions and requires a third reduction due to toxic reactions must discontinue the study treatment.

Principles of dose modifications related to anlotinib hydrochloride capsules.

- Hematologic toxicity

1. Thrombocytopenia

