14. CTCAE grade 3 fatigue, lasting for >7 days
15. CTCAE grade 3 hypertension, hand-foot skin reaction, diarrhea, nausea, and vomiting that are not relieved by symptomatic treatment until the next treatment cycle.
16. CTCAE grade 3 abnormal laboratory examinations that are not relieved by symptomatic treatment until the next treatment cycle.

If one subject experiences toxicity that met the criteria for DLT, the study treatment was interrupted and follow-up was performed as described in the study procedures. Treatment can be discontinued due to any DLT. However, under the investigator and co-sponsor approval, subjects with DLT could receive the next lowest dose level after recovery.

- 1. Efficacy assessment
     1. Primary endpoint
- **Progression-free survival:**

PFS is defined as the time from enrollment to the first time of PD or death from any cause, whichever occurs first.

If the subject did not experience disease progression or death, PFS is defined as the date of the last confirmed progression-free. Subjects who discontinued for reasons other than disease progression (no subsequent tumor imaging assessment) and starting subsequent therapy after the trial were censored at the time of discontinuation or the initiation of subsequent therapy. In cases other than those described above, pre-planned sensitivity analyses will undertake to define PFS based on the date of confirming imaging progression events. New onset other tumor is not considered indicative of PD and is not censored as data.

If the image examination and assessment show PD, the date of PD is not defined as the imaging time of first signs of PD, but the time of definite imaging evidence of PD. If the PD is diagnosed with other clinical examinations, the date of PD is defined as the diagnosis time.

- - 1. Secondary endpoints
- **OS:** OS is defined as the time from enrollment to the date of death due to any cause. For the analysis of OS, data for patients who are alive will be censored for OS at the time of the last follow-up. Data for patients who were lost to follow-up will be censored for OS at the last date they were known to be alive. Censored OS is defined as the time from randomization to censor.
- **1-year PFS rate:** 1-year PFS rate is defined as the percentage of patients who have not progressed or died at 1 year.
- **1-year OS rate:** 1-year OS rate is defined as the percentage of patients who are still alive at 1 year.

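### Section 6.3 permits a restart one anlotinib level lower after any DLT without excepting events the dose tables mark for permanent termination, and the two-reduction stop rule works only from a 12 mg start

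*Protocol*

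**What the plan says.** Section 6.3 interrupts treatment after a DLT and says treatment can be discontinued for any DLT. It then adds that "under the investigator and co-sponsor approval, subjects with DLT could receive the next lowest dose level after recovery". TQB2450 doses are in principle not modified, so the lower level means anlotinib. Section 6.3 names no excepted event and does not refer to the dose tables in Section 5.5.

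Those tables (5.5-2 to 5.5-9) give recommended actions by grade. Under the general principles for adjustment of administration regimens they can be departed from: "If the investigator determines that the dosing adjustment differs from the proposed adjustment rule, after consultation and communication with the sponsor", the investigator adjusts by guideline or experience and records why. Section 6.5.6.2 (Hypertension) says that a subject with a hypertensive crisis should stop study treatment and leave the study.

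The Dose modification section gives two steps down from 12 mg (10, then 8 mg) and one from 10 mg (8 mg). For the lowest start, "If the initial dose is 8mg, there was no down-dose selection". Its stop rule applies to a subject who has had two reductions and needs a third.

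Several general provisions surround these rules:
- The synopsis lists as a ground for mandatory termination: "Occurrence of intolerable adverse reactions or severe adverse events confirmed by the investigator". Section 4.5 lists the same ground, but under the lead-in "The investigator has the right to decide whether to withdraw from the study".
- The administration principles say that patients with disease control "who can tolerate adverse effects continue the medication until disease progression or intolerance".
- On delays: "If a subject is unable to resume treatment by day 35 after the last dose, the subject must discontinue anlotinib hydrochloride treatment".
- When anlotinib is permanently stopped for toxicity, "monotherapy with TQB2450 should be continued until disease progression or unacceptable toxicity".

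**The concern.** The restart permission covers every DLT, including some for which the protocol elsewhere recommends that anlotinib never be given again. Anlotinib is anti-angiogenic, so re-exposure after a major bleed, grade 4 thrombocytopenia or life-threatening hypertension carries a real hazard. The entry criteria already treat such events as disqualifying: grade 3 or higher bleeding within 4 weeks, and cerebrovascular accident or hypertensive crisis within 6 months. Section 6.3 asks only for recovery and two approvals, with no minimum interval.

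The stop rule raises a question of consistent handling. A 12 mg starter already reduced to 8 mg who needs a further reduction must stop. A subject who started at 8 or 10 mg and is in the same position at 8 mg gets no specific instruction, so sites may differ. The two gaps can meet in one patient: a 10 mg subject restarted at 8 mg under Section 6.3 has no further level and no specific stop rule.

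**Working it through.** **1. Termination rows against the DLT list**

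| Event | Recommended action | DLT in cycle 1 under 6.3? | Excepted from restart? |
|---|---|---|---|
| Grade 4 platelet decrease | Terminate (Table 5.5-2) | Yes, grade IV hematologic | No |
| Grade 3 or higher bleeding | Terminate (Table 5.5-6) | Yes, grade III or higher non-hematologic | No |
| Grade 4 hypertension | Terminate (Table 5.5-7) | Yes, same category | No |
| Other grade 4 non-hematologic | Terminate (Table 5.5-9) | Yes, same category | No |

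The other four tables (neutrophils, liver function, proteinuria, hand-foot skin reaction) reduce the dose at their highest grade and have no termination row. So 4 of 8 tables carry a row that Section 6.3 does not except. Section 6.5.6.2 gives hypertensive crisis as an example of grade 4 hypertension. It therefore overlaps the third row, with a firmer instruction attached.

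**2. Steps available and reach of the stop rule**

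- From 12 mg: 12 → 10 → 8, so 2 reductions.
- From 10 mg: 10 → 8, so 1 reduction.
- From 8 mg: 0 reductions.

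The rule needs 2 completed reductions and a third required. Since 1 < 2 and 0 < 2, only a 12 mg starter can meet it. All 8 tables contain a row calling for a one-level reduction, which cannot be carried out at 8 mg.

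**3. How many patients**

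Inputs: the escalation rules in Section 6.1 (Stage 1), assuming no replaced or additional subjects.

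- Cohort size: 3 if there are 0 DLTs or at least 2 among the first three; 6 if there is exactly 1.
- Total: minimum 3; maximum 3 levels × 6 = 18. This reproduces the plan's 3 to 18.
- Most DLT patients at a level that is passed: 0 of 3, or 1 + 0 of 6, so 1.
- Most at a level that is not passed: the larger of 3 (3 of 3) and 1 + 3 = 4, so 4.

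A lower level exists only below 10 mg and 12 mg. If escalation fails at 10 mg, the maximum there is 4. If 10 mg is passed and 12 mg fails, the maximum is 1 + 4 = 5. So at most 5 patients could be offered a restart, and the exception matters only for those among them with an event in the table above. At 8 mg up to 4 DLT patients are possible, but there is no lower level to restart at.

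The ladder gap concerns 3 or 6 patients at 8 mg plus 0, 3 or 6 at 10 mg, so 3 to 12 in all. How many would need less than 8 mg cannot be derived from the document.

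**The case against.** The strongest reply is that nothing here conflicts. Section 6.3 says a subject could restart, not must, and only after recovery and two approvals. The tables are recommendations that may be departed from after consulting the sponsor, so re-exposure is possible even without Section 6.3. The synopsis requires termination for intolerable or severe events, and hypertensive crisis has its own instruction. On the ladder, someone who cannot tolerate the lowest dose is naturally intolerant and stops on that ground.

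Much of this stands. A reader might infer that the protocol issues two contradictory orders. It does not: one text is permissive and the other advisory, and what is missing is an exception. A reader might also take the wording of the stop rule, which refers to study treatment, to leave open whether TQB2450 stops too. The general principles largely settle that by continuing TQB2450 alone.

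Two parts of the reply do not close the matter. First, the general termination ground does not mark the limit of Section 6.3. Read strictly it would cover most DLTs and leave the restart clause almost no use, and Section 4.5 makes the same ground discretionary. Second, Section 6.3 is a separate route: it needs approval from the investigator and co-sponsor, while departures from the tables go through the sponsor. On the ladder, the day-35 rule covers only subjects who cannot resume in time. A subject who recovers at 8 mg from, say, a grade 2 or 3 event under Table 5.5-9 is told to reduce and has nowhere to go.

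**Conclusion.** The point holds as a minor patient-safety inconsistency that is cheap to remove. Section 6.3 lacks an exception for four event categories that the protocol's own anlotinib tables mark for permanent termination, and for hypertensive crisis. The stop rule gives no specific instruction to 8 or 10 mg starters, for whom general intolerance criteria are the only backstop.

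Its reach is small: at most 5 phase I patients for the restart clause, fewer once limited to listed events, and a pool of 3 to 12 for the ladder gap. These counts assume that the escalation rules are followed without replacement and that the restart clause belongs to the escalation stage.

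Two wider inferences are not supported. The point does not touch MTD determination, sample size or the PFS analysis: the escalation rules count a DLT whether or not the subject later restarts. Nor does the ladder gap reach the 54 phase II patients as the synopsis now stands, because it sets 12 mg, where the stop rule works. It would reach them only if 8 or 10 mg were carried forward, which Section 6.1 provides for.

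**What to change.** In Section 6.3, replace the restart sentence with:

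*With investigator and co-sponsor approval, a subject who has recovered from a DLT may restart at the next lower anlotinib level, if one exists, unless the event is one for which anlotinib Tables 5.5-2 to 5.5-9 state permanent termination (grade 4 platelet decrease, grade 3 or higher bleeding, grade 4 hypertension, other grade 4 non-hematologic toxicity attributed to anlotinib) or is a hypertensive crisis.*

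Naming the anlotinib tables matters. A reference to all Section 5.5 tables would also take in Tables 5.5-1 and 5.5-10, and could bar anlotinib after a TQB2450 reaction for which the general principles continue anlotinib alone. Events attributed to TQB2450 stay under those two tables and the general principles. The general allowance for departing from the adjustment rules need not be changed.

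In the Dose modification section, replace the stop rule with:

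*A subject who needs a reduction below 8 mg because of toxicity must permanently discontinue anlotinib; TQB2450 is then handled under the general principles.*

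This works from every starting dose and removes any doubt about which drug stops.

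The cost is two sentences, with no added patients, visits or tests. There are two downsides. Some 8 or 10 mg starters with a recoverable event would lose anlotinib, as a 12 mg starter already reduced to 8 mg does now. And Section 6.3 would lose its discretion for the listed events.

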- **Duration of response (DOR):** DOR is defined as the time from first documented evidence of complete response (CR) or partial response (PR) until PD or death, whichever occurred first. For the analysis of DOR, data for patients who discontinue study due to due to reasons other than disease progression (without subsequent imaging examinations) or hose who received post-trial treatment will be censored at the time of study discontinuation or the initiation of post-trial treatment. The occurrence of newly developed other tumors is not considered as a PD event, and will be not censored.
- **Disease control rate (DCR):** DCR is defined as the percentage of subjects with PR, CR, or stable disease (SD) lasting for ≥4 weeks.
- **Objective response rate (ORR):** ORR is defined as the percentage of subjects with confirmed tumor volume reduction to pre-specified values and maintenance of minimum time requirements (≥4 weeks), including subjects with a PR or CR. Objective responses are assessed per RECIST v1.1. Subjects must have at least one measurable lesion at baseline. The response was classified as CR, PR, SD, and PD according to RECIST v1.1.
  1. Safety assessment
     1. Safety management

Various management will be taken to ensure the safety of subjects in the study, including strict inclusion and exclusion criteria and close monitoring (hospitalization monitoring, follow-up, and out-of-hospital diary card recording and telephone follow-up).

Safety is analyzed in the safety analysis set (SAS).

- - 1. Adverse events

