**8.2.1 Sample size**

Phase I: Following the 3+3 principle of dose adjustment, a minimum of 3 and a maximum of 18 patients were expected to be enrolled.

Phase Ⅱ: The mPFS of TQB2450 plus anlotinib hydrochloride capsules was estimated to be 9 months, and the historical control group carboplatin combined with pemetrexed was set as 5 months. The two-sided test level α was 0.05, and the power level was 0.90. It was calculated that 54 subjects would need to be enrolled (considering that the loss to follow-up rate should be controlled at 20%). The study was expected to last 24 months, including 12 months after enrollment. At the end of the study, 32 end-point events were expected to have occurred.

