If the subject did not experience disease progression or death, PFS is defined as the date of the last confirmed progression-free. Subjects who discontinued for reasons other than disease progression (no subsequent tumor imaging assessment) and starting subsequent therapy after the trial were censored at the time of discontinuation or the initiation of subsequent therapy. In cases other than those described above, pre-planned sensitivity analyses will undertake to define PFS based on the date of confirming imaging progression events. New onset other tumor is not considered indicative of PD and is not censored as data.

If the image examination and assessment show PD, the date of PD is not defined as the imaging time of first signs of PD, but the time of definite imaging evidence of PD. If the PD is diagnosed with other clinical examinations, the date of PD is defined as the diagnosis time.

- - - 1. **Analysis of secondary efficacy endpoints**

OS is defined as the time from enrollment to the date of death due to any cause. For the analysis of OS, data for patients who are alive will be censored for OS at the time of the last follow-up. Data for patients who were lost to follow-up will be censored for OS at the last date they were known to be alive. Censored OS is defined as the time from randomization to censor.

One-year progression-free rate is defined as the probability of patients experiencing the endpoint events of disease progression from enrollment to one year. Endpoint events include disease progression, death, and withdrawal due to intolerance.

One-year survival rate is defined as the probability of patients experiencing the endpoint event of death from enrollment to one year.

DOR is defined as the time from the date of CP and PR until the date of disease progression. Subjects who discontinued for reasons other than disease progression (no subsequent tumor imaging assessment) and starting subsequent therapy after the trial were censored at the time of discontinuation or the initiation of subsequent therapy. New onset other tumor is not considered indicative of PD and is not censored as data.

DCR is defined as the percentage of subjects with PR, CR, or SD lasting for ≥4 weeks.

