ORR is defined as the percentage of subjects with confirmed tumor volume reduction to pre-specified values and lasting for ≥4 weeks, including subjects with a PR or CR. Objective responses are assessed per RECIST v1.1. Subjects must have at least one measurable lesion at baseline. The response was classified as CR, PR, SD, and PD according to RECIST v1.1.

For PFS, OS, and DOR, Kaplan-Meier was used to estimate median survival and draw survival curves, and the 1-year disease progression rate and 1-year survival rate were also estimated. For ORR and DCR, the Clopper-pearson method was used to estimate 95% confidence intervals.

1. **Project management**
   1. **Information promulgation**

The present study will be registered and publicized in the Chinese Clinical Trial Registry after obtaining ethical approval from the responsible unit of the clinical study.

- 1. **GCP and ethics committee review and approval**

This clinical trial will be conducted in accordance with the Declaration of Helsinki (2013), the GCP promulgated by the NMPA and related regulations. The investigator will not begin any study subject activities until approval from the Clinical Research Ethics Committee of the Clinical Trial Team leader. Any modifications of the protocol during the clinical study should be declared and filed to the Ethics Committee.

Clinical investigators will follow all applicable regulations to protect subjects. The informed consent document used in the trials must be reviewed by the sponsor, approved by the ethics committee, and available for inspection.

- 1. **Informed consent**

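### Sections 6.4.2 and 8.2 give two different rules for duration of response: they disagree on whether death counts and on whom to censor, and neither limits censoring to patients without prior PD or death

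*Protocol*

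**What the plan says.** Section 6.4.2 (Secondary endpoints) runs DoR from first documented CR or PR "until PD or death, whichever occurred first". It then censors two groups. The first is patients who discontinue for reasons other than progression and have no later imaging. The second is introduced with "or hose who received post-trial treatment will be censored at the time of study discontinuation or the initiation of post-trial treatment".

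The analysis of secondary efficacy endpoints in section 8.2 (8.2.6.2 by sequence) gives another definition: "DOR is defined as the time from the date of CP and PR until the date of disease progression". Death is not named. Its censoring sentence reads "Subjects who discontinued for reasons other than disease progression (no subsequent tumor imaging assessment) and starting subsequent therapy after the trial were censored", and two alternative censoring dates follow: discontinuation or the start of subsequent therapy. The PFS definition in section 6.4.1 uses the same 'and' sentence.

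The Synopsis termination criteria end study participation at "Disease progression (PD) determined according to RECIST 1.1 criteria or considered clinically progressive". The estimator is stated in section 8.2: "For PFS, OS, and DOR, Kaplan-Meier was used to estimate median survival and draw survival curves".

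**The concern.** Two features of the text cause trouble.

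- **Event.** One section counts death without progression as the end of a response and the other does not.
- **Censoring.** Section 6.4.2 joins its two groups with 'or', and the post-trial-treatment group carries no condition that PD or death has not already occurred. The analysis section joins the conditions with 'and', which can be read as requiring both.

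The phase II part is single-arm, so DoR will be read as an absolute duration, with no comparator sharing any distortion. A programmer following one section can obtain a different median from one following the other on the same data. DoR is secondary under section 6.4.2, although the Synopsis lists it first among the primary effect endpoints.

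**Working it through.** **Design figure.** The protocol gives no planning figure for DoR. Its only design calculation is for PFS: medians of 5 and 9 months, 12 months of accrual in a 24-month study, 20% dropout, and "The two-sided test level α was 0.05, and the power level was 0.90".

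- Events: (1.960 + 1.282)² / [ln(5/9)]² = 10.51 / 0.3455 = 30.4, so 31.
- Event probability with λ = ln 2 / 9: 1 − (e^(−12λ) − e^(−24λ)) / (12λ) = 0.741.
- 43 evaluable × 0.741 = 31.9, matching the stated 32 events; 43 / 0.80 = 53.75, matching N = 54.
- Power with 32 events is 0.914.

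The design reproduces and uses no DoR quantity.

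**The two DoR rules applied to the same responder.**

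| Responder | 6.4.2, earlier date counts | 6.4.2, taken literally | Analysis section of 8.2 |
|---|---|---|---|
| Progresses, stops, then starts new therapy | Event at PD | Censored | Event at PD if 'and' requires both conditions; as 6.4.2 if 'and' lists two groups |
| Dies on treatment without PD | Event at death | Event at death | Not an event |
| Stops for toxicity, still scanned, no new therapy, dies without PD | Event at death | Event at death | Not an event |
| Stops for toxicity, still scanned, starts new therapy, dies without PD | Censored before death | Censored before death | Not an event; if 'and' requires both conditions, no censoring date is given |

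Rows two and three differ however the censoring sentences are parsed. In row four, if 'and' requires both conditions, the same death is a PFS event under 6.4.1 but not a DoR event.

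**Size.** All inputs here are assumptions:

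- exponential DoR with true median 6 or 9 months;
- data cut-off 9 to 21 months after response;
- 10% of events are deaths;
- 10% of responders subject to early non-PD discontinuation;
- new therapy 0.5 to 2 months after PD.

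Each setting was simulated with 60,000 responders, so the figures are large-sample Kaplan-Meier medians.

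*Death not counted.* The remaining hazard is 0.9 of the total, so the median becomes 6 / 0.9 = 6.7 or 9 / 0.9 = 10.0. The simulation gives 6.6 to 6.7 and 9.9 to 10.1.

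*6.4.2 with the earlier date counting.* No PD event is lost. The medians are 6.0 and 8.9 to 9.1.

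*6.4.2 taken literally (a progressor treated later is censored at therapy start).*

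| Progressors treated later | Events kept (true median 6 / 9) | Median, true 6 | Median, true 9 |
|---|---|---|---|
| 30% | 74% / 74% | 8.5 | 12.5 |
| 50% | 56% / 57% | 11.4 | 16.2 |
| 70% | 39% / 40% | 16.0 | 20.3 |
| 90% | 22% / 23% | 20.5 | not reached |

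As a check, the share kept should be slightly above 1 − 0.9q for treated share q, because some therapy starts after the cut-off. This gives 73%, 55%, 37% and 19%.

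**The case against.** A reader might infer from the 'or' sentence that every responder treated after progression is censored, so that most DoR events vanish and the median is inflated. The documents do not support this. The definition in 6.4.2 already stops the clock at PD or death. Progression ends study treatment, so post-trial therapy in a progressor normally starts afterwards, and a censoring date later than the event has no effect in a Kaplan-Meier analysis. Nothing says that an observed PD is to be overwritten. The literal-reading table shows what would follow from such programming, not what the plan requires. Its driving input, the subsequent-therapy rate, is not in the protocol.

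It can also be said that 'and' merely lists two groups, matching the two alternative censoring dates, so that the sections agree on censoring. That is a fair parse. The group without a 'before PD or death' limit then also appears in the analysis section and in the PFS sentence, so the limit is still needed.

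Third, a PD after new therapy would rarely be recorded, because the imaging notes to the schedule stop scheduled tumour assessment when new treatment begins. That stands for PD. It does not stand for death, since survival follow-up continues until death.

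Finally, DoR supports no test or decision rule. That is correct and limits the importance of the point. None of these arguments removes the disagreement on death.

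**Conclusion.** The protocol fixes two DoR rules that can give different results. The disagreement on death is on the face of the text. With deaths at an assumed 10% of events it moves the median by roughly a tenth: 6 to about 6.7 months, or 9 to about 10.

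The censoring sentence in 6.4.2 is incomplete rather than plainly biased. On the ordinary earliest-date reading no PD event is lost. Only if it were programmed literally could progressors treated later be censored and the median lengthened. Under that reading most events are lost only when more than roughly half of progressors receive later therapy, so a general claim that DoR is inflated goes beyond the documents.

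The consequence is confined to DoR, a secondary endpoint by 6.4.2. The 54 patients, the 32 expected events and the primary PFS comparison are not affected by the DoR correction.

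**What to change.** State one DoR rule in section 6.4.2 and repeat it in the analysis section of 8.2:

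- **Event:** PD or death from any cause, occurring before any new anti-tumour therapy.
- **Censoring:** only responders who start new anti-tumour therapy or leave follow-up without prior PD or death, using the same censoring-date convention as for PFS.
- Remove the free-standing clause on post-trial treatment from 6.4.2, and name death in the analysis section.

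Put the same 'without prior PD or death' limit in the PFS censoring sentence, in 6.4.1 and in section 8.2, so that the two endpoints treat the same patient alike. Say there, once for both endpoints, whether a patient who stops tumour imaging but is still followed for survival counts as having left follow-up, and which of the two stated dates applies.

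The cost is a wording change to the DoR and PFS definitions in two sections. It needs no new data collection and no change to the sample size.
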